### Intervention

Patients will receive either MST, administered at a frequency of 100 Hz with 100% of the maximum device power for a duration of 10 seconds, or bitemporal ECT, according to routine clinical practice at SMHC following the ECT clinical practice guideline in China. The electrical stimulation wave width will be 0.5 ms. The energy of electrical stimulation will be determined according to the patients’ age(age × 0.8 × 100%) and increased by 5% until a proper seizure (seizure duration of 15 seconds or longer) is achieved.

### Anesthesia

The MST/ECT procedure will be conducted under general anesthesia, which will include intravenous administration of etomidate (0.21–0.3 mg/kg) and propofol (1.82–2.44 mg/kg). Intravenous succinylcholine (1 mg/kg) will be administered as a muscle relaxant, while intravenous atropine (0.5 mg) will be administered to reduce airway secretions.

### ECT and MST procedures

For the ECT group, a Thymatron System IV device (Somatics LLC, USA) will be used with bilateral (BL) electrode placement. This configuration is selected because it represents the most commonly adopted ECT modality in majority of psychiatric hospitals in China. The MST will be delivered with NS 7000S (Wuhan Yiruide Medical Equipment New Technology Co., Ltd.) using a round coil (125-mm diameter) positioned on the vertex. At 100% output and 100 Hz frequency, the device generates a peak magnetic field strength of 3.0 T and a pulse width of 350 μs. Compared to the MagPro MST system, which uses a dual-coil design with 2.0 T surface strength and 370 μs biphasic pulses, the YIRUIDE NS 7000s offers higher peak field strength and slightly shorter pulse width, potentially enhancing seizure induction efficiency in preclinical practice.

For ECT, the pulse width of the electrical stimulus will be set to 0.5 ms. Seizure threshold titration is the primary method for determining dosage: at the first treatment session, the psychiatrist and anesthetist will administer gradually increasing stimuli until the minimum charge required to induce a 25-second EEG seizure is identified (titration method). This threshold guides the initial supra-threshold dosage (1.5× threshold) for subsequent sessions. As a secondary reference in line with local clinical practice, the initial energy dosage may also be estimated using an age-based formula (age × 0.8 × 100%) for the first session, but this is adjusted based on titration results. For subsequent sessions, dosage will be increased by 5% increments if seizure duration is inadequate (<25 s); in cases of persistent suboptimal seizures, the maximum tolerated dosage will be administered. This approach prioritizes individualized titration to balance efficacy and safety, while exploring the utility of age-based estimates for resource-constrained settings. Additionally, we will monitor data to explore the empirical ‘half-age’ method (38) for future reference.

MST will be conducted at 100 Hz and 100% output using a pulse width of 350 μs and a peak intensity of the magnetic field at 3.0 Tesla. The duration of magnetic stimulation will be titrated using a 10-second train duration, starting from 2 seconds and increasing by 4 seconds in subsequent sessions, up to a maximum of 10 seconds (i.e., 200–1,000 pulses per session). In cases of poor seizure quality (<15 s), the stimulation duration increment will be set to 6 seconds in the next session. If no seizures were elicited, an additional 10-second stimulation will be administered immediately. Subsequent MST treatments will be maintained at a 10-second duration for a total of 1000 pulses.

EEG recordings during MST and ECT will be obtained using the Thymatron IV device with left and right frontal leads.

Patients will undergo identical preparation procedures, including the placement of earplugs and skin preparation for ECT electrode placement, irrespective of treatment allocation. To maintain blinding, the auditory stimulus from a recorded MST session will be played during ECT administration to prevent treatment allocation disclosure to individuals in adjacent rooms.

Completers will be defined as patients who received at least 8 treatments or achieved remission before the eighth treatment. Relapse will be defined as an HDRS-24 total score of 16 or higher, with at least a 10-point increase in HDRS-24 score sustained across two visits at least 1 week apart, the emergence of psychotic or suicidal symptoms, or the need for readmission to inpatient care.

While 12 sessions are standard for acute-phase treatment, the potential need for more sessions in MST will be explored through *post-hoc* analyses. This trial’s design prioritizes comparability with ECT’s typical acute regimen while allowing for long-term outcome assessment to capture delayed benefits.

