One notable limitation is the use of an age-based dosing method for ECT (80% of the patient’s age in years × 100 mC), which is less precise than seizure threshold titration. This approach may lead to suboptimal dosing in some patients, such as underdosing in younger individuals with higher seizure thresholds or overdosing in older adults with lower thresholds, potentially increasing the risk of cognitive side effects or reducing treatment efficacy. The decision to use age-based dosing reflects common clinical practice in many Chinese centers, where titration protocols are not yet universally adopted due to resource constraints or training variability. While this aligns with real-world settings, it introduces variability in ECT dosing that could affect the comparability of safety and efficacy outcomes with MST. Future studies using more personalized dosing strategies (e.g., titration) are needed to validate the generalizability of our findings. An additional limitation is the absence of a dedicated autobiographical memory test in our cognitive assessment battery. Autobiographical memory is a domain frequently reported to be sensitive to ECT-mediated cognitive impairments, and its exclusion may limit our ability to fully capture differences in this specific memory function between MST and ECT. Future studies are encouraged to incorporate validated autobiographical memory measures to complement assessments of verbal learning and memory and provide a more comprehensive evaluation of cognitive effects.

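### The protocol gives contradictory rules for dosing the ECT comparator (titration or age formula, per cent or mC, 15 s or 25 s) and, to a lesser degree, for the early MST sessions

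*Protocol article*

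**What the plan says.** **ECT, Intervention section.** The dose follows age: "The energy of electrical stimulation will be determined according to the patients’ age(age × 0.8 × 100" (the formula ends in a per cent sign). It is then "increased by 5% until a proper seizure (seizure duration of 15 seconds or longer) is achieved". Titration is not mentioned.

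**ECT, ECT and MST procedures section.** "Seizure threshold titration is the primary method for determining dosage". Stimuli are raised at the first session "until the minimum charge required to induce a 25-second EEG seizure is identified (titration method"). Later sessions start from 1.5 times the threshold found in this way. Seizures under 25 s are inadequate and lead to 5% increments. The age formula appears only as a secondary reference that may be used for the first session and is then adjusted to the titration result.

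**ECT, Discussion (limitations).** "One notable limitation is the use of an age-based dosing method for ECT". The formula is given there as 80% of age in years times 100 mC. The method is called less precise than titration, and titration is left to future studies. The same paragraph says that the resulting variability in ECT dosing could affect comparability with MST.

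**MST.** The Intervention section has MST "administered at a frequency of 100 Hz with 100% of the maximum device power for a duration of 10 seconds". The ECT and MST procedures section has the train "starting from 2 seconds and increasing by 4 seconds in subsequent sessions, up to a maximum of 10 seconds", with a 6-second step after a seizure shorter than 15 s. If no seizure occurs, an extra 10-second stimulation is given at once. Later treatments are held at 10 seconds and 1,000 pulses.

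**The concern.** The trial is designed to show non-inferiority to ECT on HDRS-24, and it also aims to show better preserved verbal memory on HVLT-R. Both conclusions are relative to the ECT that is delivered, so the protocol needs one definition of it. Here the operating sections disagree with each other, and the Discussion disagrees with the more detailed of the two.

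The direction matters for both primary outcomes. If ECT were less effective than intended, non-inferiority of MST would be easier to conclude. If ECT caused more cognitive harm than intended, an HVLT-R advantage for MST would be easier to conclude. The Discussion itself names reduced efficacy and increased cognitive side effects as possible results of suboptimal dosing under the age-based method. It also says that titration is not universally adopted in Chinese centers. With seven sites working from this text, each could follow a different section and still be within protocol.

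**Working it through.** The protocol states no dose figure that can be reproduced, and its sample size does not depend on dose. The check sets the sections side by side and does arithmetic on their own rules.

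**1. ECT rules compared**

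| Item | Intervention | ECT and MST procedures | Discussion |
|---|---|---|---|
| Method | Age formula | Threshold titration, then 1.5 times threshold; age formula optional at session 1 | Age formula; titration left to future studies |
| Quantity | Energy, per cent | Charge for the threshold; energy, per cent, for the age formula | mC |
| Adequate seizure | 15 s or longer | 25 s EEG seizure to define threshold; under 25 s inadequate later | Not stated |

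There are two methods, age-based and titrated. The procedures section and the Discussion cannot both describe the method of this trial. A titrated dose depends on the measured threshold, so it cannot be derived from the age formula.

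**2. Age formula**, over the 18 to 65 range in the Inclusion criteria

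- Per cent form, age × 0.8: 18 × 0.8 = 14.4; 65 × 0.8 = 52.
- mC form, 0.8 × age × 100: 0.8 × 18 × 100 = 1,440 mC; 0.8 × 65 × 100 = 5,200 mC.

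These are different quantities. The document gives no conversion between them.

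**3. Seizure adequacy.** An ECT seizure of at least 15 s but shorter than 25 s is proper under the Intervention section and triggers a dose increase under the procedures section. This assumes the same measure in both places: the procedures section specifies an EEG seizure for titration, and the Intervention section names no measure.

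**4. MST pulses**, at 100 Hz (100 pulses per second) over 12 sessions

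- Fixed 10 s: 12 × 10 × 100 = 12,000.
- Steps of 4 s (2, 6, then 10 s ten times): (2 + 6 + 100) × 100 = 10,800; 10,800 / 12,000 − 1 = −10%.
- 6-second step after a short first seizure (2, 8, then 10 s ten times): (2 + 8 + 100) × 100 = 11,000; −8.3%.
- No seizure at session 1, with the extra 10 s given and 10 s held from then on: (2 + 10 + 110) × 100 = 12,200; +1.7%.

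Session 1 is therefore 1,000 pulses under one section and 200 under the other, unless the no-seizure branch applies. From session 3 both sections give 10 s.

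**The case against.** **Randomization protects the comparison.** Allocation is by permuted blocks, 1:1, at each site, so a site that doses ECT differently does not unbalance the arms. This stands. A reader might infer that the comparison loses its reference altogether, and the document does not support that. What is missing is a single definition of the ECT arm.

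**No divergence is shown.** The Intervention section points to routine practice at one center under a national guideline, and both operating sections raise the dose by 5% when a seizure is inadequate. This stands too: the text permits different practice but does not show it, and no bias can be computed. It does not remove the conflict over method and cut-off.

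**The Discussion is not an operating instruction.** This is fair as regards the mC figure, which may be loose wording; the 1,440 to 5,200 range is literal arithmetic on it and not evidence of a rival site instruction. A reader might count three incompatible ECT methods, but there are two. Even without the Discussion, the Intervention and procedures sections conflict.

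**The MST sections can be read together.** The Intervention section may summarise the maintained setting and the procedures section give the lead-in. This largely stands, and it makes the MST point minor.

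**Different re-dosing cut-offs by arm** (under 25 s for ECT, under 15 s for MST) might be read as a further contradiction. They are separate rules for two modalities, and nothing in the document says they must match.

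**Conclusion.** The contradiction in ECT dosing holds and sits in current text. Method, units and seizure-adequacy criterion each have more than one answer, so the comparator of a non-inferiority trial is not defined in one way. The adequacy conflict assumes that both sections mean the same seizure measure. The MST inconsistency is lesser: it falls mainly on the first two sessions, at about 8 to 10% fewer pulses in total, and the shortfall disappears if no seizure is elicited at session 1.

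The consequence is one of interpretation. A reader of the result could not say which form of ECT MST was compared with, and the Discussion concedes that dosing variability could affect comparability. The size and direction of any effect on HDRS-24 or HVLT-R cannot be derived from the document, and the sample size is unaffected.

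**What to change.** Reconcile the Intervention section, the ECT and MST procedures section and the Discussion limitation into one instruction per arm. Each should state the dosing method, the units, the seizure-adequacy criterion and how the seizure is measured, and should bind all seven sites. Which rule applies is for the clinical leads; no view is taken here.

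The Study settings section gives a start date of 1 December 2024, so patients may already have been treated. Establish which method was used for them, and report dosing method and delivered dose by arm and site beside the primary result.

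The cost is a protocol clarification, a letter to sites and possibly some retrospective data retrieval. The article does not say whether delivered dose and seizure duration are recorded at every session, so the retrieval effort is unknown. If the clarification changes practice at a site in mid-trial, the date of change should be recorded so that patients treated before and after it can be told apart.

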### Patient safety

We implement proactive site monitoring and adhere to established safety protocols as standard procedures in our previous ECT/MST studies (26, 27). Electrophysiological recordings pose no known risks, and there is no evidence of short- or long-term side effects associated with them. However, a small proportion of participants may experience scalp discomfort during the procedure. In the afternoon following each treatment session, patients will be interviewed using the Columbia ECT Subjective Side Effects Schedule (39) to assess subjective adverse effects. Patients will be asked to report the presence (scored as 0 for absent and 1 for present) and severity (scored as 0 for no perceived adverse effect, 1 for mild, 2 for moderate, and 3 for severe) of various adverse effects. Additionally, any potential severe adverse events will be meticulously documented by the experimenter.

### Additional treatments

As the primary objective of this trial is to evaluate efficacy, participants are restricted from receiving concurrent treatments for their depressive symptoms, except for one type of antidepressant medication, during the 30-day intervention period. However, the use of psychoactive medications and psychotherapy is allowed during the 12-week follow-up period, with detailed documentation of the type, dosage, and frequency/session of medication or psychotherapy.

During the 12-week follow-up period, participants may receive maintenance ECT, pharmacotherapy (e.g., antidepressants, mood stabilizers), or psychotherapy to prevent relapse. The type, dosage, and frequency of maintenance treatments will be recorded in detail to assess their impact on outcomes.

### Withdrawal criteria

Criteria for participant withdrawal from the study comprise the following: 1) Failure to complete a minimum of 8 ECT/MST treatment sessions within the designated 30-day period. Participants missing scheduled sessions may reschedule them at their convenience, but failure to complete the required sessions will result in dropout status. 2) Voluntary withdrawal of consent for ECT/MST treatment by the participant. 3) Experience of a severe adverse event with significant distressing consequences, such as seizures, skin burns, or blisters. Withdrawn participants will continue to be monitored, and outcome measures will be conducted to the extent possible.

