### Sample size estimation

The sample size calculation for this study was conducted through *a priori* power analysis using G*Power 3.1.9.7 (29). Parameters were chosen, including α = 0.05 and power (1-ß) = 0.95. An effect size of f = 0.1 was selected based on previous research findings (15). Specifically, in the intent-to-treat sample (N = 73), 18 participants (51.4%) in the MST group (N = 35) and 16 (42.1%) in the ECT group (N = 38) met response criteria, while 13 (37.1%) in the MST group and 10 (26.3%) in the ECT group met remission criteria. In addition to the two experimental conditions (MST and ECT), covariates including age, sex, duration of illness, age of onset, intelligence quotient (IQ), and antidepressant usage were considered, resulting in a total of 6 covariates. Accounting for a potential dropout rate of 20%, the final estimated number of participants required for the study was determined to be 210. (**Figure 2**).

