**Figure 2 f2:**
[figure not shown]
G*Power-based sample size calculation for a repeated-measures ANOVA with a within-between interaction. The plot depicts an *a priori* power analysis to determine the required sample size for a repeated-measures analysis of variance examining the interaction between a between-subjects factor (2 groups) and a within-subjects factor (6 measurement time points). The upper panel shows the central F-distribution under the null hypothesis (red solid curve) and the noncentral F-distribution under the alternative hypothesis (blue dashed curve). The critical F-value (2.22502) is indicated by the green vertical line. The red shaded region represents the α error probability (Type I error, set at 0.05), and the blue shaded region denotes the β error probability (Type II error), with power (1−β) targeted at 0.95. Input parameters include: effect size (f) = 0.1, α = 0.05, number of groups = 2, number of repeated measurements = 6, correlation among repeated measures = 0.5, and sphericity correction (ϵ) = 1. Output parameters reveal a total required sample size of 166, a noncentrality parameter (λ) of 19.92, numerator degrees of freedom (df) = 5, denominator df = 820, and an actual power of ~0.95.

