### Outcomes

#### Primary outcome

The primary outcome measure is the change in HDRS-24 total score from baseline to the 12-week follow-up, which is assessed after the completion of the 12-session acute treatment phase (conducted over 4 weeks) and a subsequent 12-week post-treatment observation period. A reduction of at least 50% in the HDRS-24 score indicated a response to treatment, while a reduction of at least 60% in the HDRS-24 score and a total score of 8 or less indicated remission. Change in HVLT-R total recall score from baseline to the 12-week follow-up (assessing verbal memory, a key cognitive domain sensitive to seizure therapy effects).

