## Data entry and analyses

This trial aims to provide replicated evidence that MST is as effective as ECT in terms of remission rates, response rates, and reduction of depressive symptoms (assessed by the primary outcome: change in HDRS-24 from baseline to 12-week follow-up after the acute treatment phase) and superior in preserving verbal memory (via HVLT-R as an additional primary outcome), with fewer physical and cognitive side effects overall. Additionally, this study will explore personalized electrophysiological indicators (EEG/ECG) in an exploratory manner to inform future individualized treatment decisions for ECT and MST, and to generate hypotheses about the physiological mechanisms underlying the antidepressant efficacy and cognitive effects of MST/ECT. To our knowledge, this will be the largest RCT comparing ECT and MST in China. The trial will provide evidence to determine whether individualized treatment decisions based on personalized electrophysiological characteristics hold promise for optimizing the balance between efficacy and side effects (40). Specifically, it will offer insights into the potential effect sizes, acceptability, feasibility, and safety of the novel interventions under investigation. Predicting efficacy and side effects based on physiological characteristics, such as indicating greater side effects with ECT and comparable efficacy but fewer side effects with MST for patients with MDD, suggests that MST may be more suitable for these patients. Alternatively, physiological characteristics indicating superior efficacy with ECT compared to MST, with comparable side effects between the two, suggest that ECT may be more appropriate for these patients.

Firstly, data entry will undergo a thorough double-check to ensure accuracy. Data quality will then be assessed, with particular attention given to data distribution, and outliers will be excluded from subsequent analysis. Once data integrity is confirmed, detailed analyses of primary and secondary outcomes will be conducted using IBM SPSS Statistics 20 for Windows (Armonk, NY: IBM Corp).

Descriptive statistics, such as mean and standard deviation, will be computed for each study arm separately. Analyses will be performed within the intention-to-treat (ITT) framework to assess the effectiveness of interventions for all participants, utilizing multiple imputed datasets to address missing data.

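### Withdrawal criterion 1 has no remission exception, so a patient who remits and stops before session 8 is both a completer and a dropout

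*Protocol article*

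**What the plan says.** Two sections of the protocol article classify patients by the same threshold of 8 sessions.

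- **ECT and MST procedures:** "Completers will be defined as patients who received at least 8 treatments or achieved remission before the eighth treatment". Remission is an alternative route to completer status.
- **Withdrawal criteria, item 1:** "Failure to complete a minimum of 8 ECT/MST treatment sessions within the designated 30-day period" is a ground for withdrawal. Missed sessions may be rescheduled, but "failure to complete the required sessions will result in dropout status". Remission is not mentioned.

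The Withdrawal criteria section then sets the follow-up of anyone withdrawn: "Withdrawn participants will continue to be monitored, and outcome measures will be conducted to the extent possible".

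The endpoint that this follow-up must reach is given under Primary outcome: "The primary outcome measure is the change in HDRS-24 total score from baseline to the 12-week follow-up". The same section defines remission as an HDRS-24 reduction of at least 60% together with a total of 8 or less.

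**The concern.** The two rules give opposite labels to one kind of patient: someone who remits and stops before the eighth session. This is also the only kind of patient for whom the remission clause in the completer definition does any work, because anyone with 8 or more sessions is a completer without it. Criterion 1 thus cancels the clause in exactly the case it was written for.

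Two things are at stake.

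- **Reporting.** Dropout counts by arm would combine patients who stopped because they were well with patients who did not tolerate or attend treatment. The Data entry and analyses section says of the trial that "it will offer insights into the potential effect sizes, acceptability, feasibility, and safety of the novel interventions under investigation", and a dropout count is a natural measure of acceptability and feasibility.
- **Follow-up.** A withdrawn patient is assessed under a weaker commitment than one who stays on schedule. Early remitters are needed at Week 12 for the primary endpoint. They are also needed at the follow-up visits for the relapse outcome, which requires worsening sustained across two visits.

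**Working it through.** **1. Can the case arise?** The Clinical measures section has the HDRS-24 rated after sessions 3, 6, 9 and 12. In Table 1 the sessions fall on Days 1, 2, 3, 5, 7, 9, 12, 15, 18, 22, 26 and 30. Session 3 is therefore on Day 3, session 6 on Day 9 and session 8 on Day 15. Two scheduled ratings precede session 8, so remission can be documented in time.

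**2. The rules side by side.**

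| Patient | Completer definition | Withdrawal criterion 1 | Conflict? |
|---|---|---|---|
| 8 or more sessions in 30 days, remitted or not | Completer | Not withdrawn | No |
| Fewer than 8 sessions, no remission | Not a completer | Withdrawn, dropout | No |
| Remits before session 8, continues to 8 or more in 30 days | Completer | Not withdrawn | No |
| Remits before session 8 and stops | Completer | Withdrawn, dropout | **Yes** |

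Only the last row conflicts, and no other section of the article reconciles it.

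**3. When does criterion 1 take effect?** Missed sessions can be made up, so failure is settled only as the 30-day window runs out. From then on the early remitter is a withdrawn participant, and the post-treatment visits, including Week 12, fall under the weaker follow-up commitment.

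**4. Does it touch the sample size?** First, the plan's own figure, with inputs from Sample size estimation and Figure 2: f = 0.1, 2 groups, 6 measurements, correlation 0.5, epsilon 1, alpha 0.05, power 0.95.

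- Noncentrality: f² × N × m / (1 − ρ) = 0.01 × 166 × 6 / 0.5 = 19.92.
- Degrees of freedom: (2 − 1)(6 − 1) = 5 and (166 − 2)(6 − 1) = 820.
- Critical F = 2.22502 and power = 0.9501 (N = 164 gives 0.947).

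This matches the figure legend: "Output parameters reveal a total required sample size of 166". Inflating for 20% dropout gives 166 / (1 − 0.20) = 207.5, or 208. The planned 210 is 7 centres × 30. The stated 20% thus allows for about 208 − 166 = 42 losses, and the other two places bring the total to 30 per centre.

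That allowance covers missing outcome data. An early remitter who is assessed at Week 12 supplies the outcome and uses none of it, whatever the label. Adding the exception leaves 166, 208 and 210 unchanged.

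**5. Size of the reporting effect.** With 105 patients per arm, each early remitter counted as a dropout adds 1 / 105 = 0.95 percentage points to that arm's reported dropout rate. The article gives no figure for how many patients will remit and stop before session 8, so no total can be computed.

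**The case against.** The strongest reply has four parts.

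- **No rule says that remitters stop.** The article fixes a 12-session course and contains no stopping rule for remission. This is correct, and it may keep the number of affected patients low. It does not remove the conflict, because the completer definition expressly provides for patients who remit and have fewer than 8 treatments.
- **The rules can be read together.** The completer definition could be taken to inform which sessions are required under the withdrawal rule. That is a sensible intention, but item 1 states the requirement itself as a minimum of 8 with no exception. A site applying it literally would withdraw the patient. Nor is this a detail merely left to a fuller document: two stated rules disagree, and sites apply withdrawal status during the trial.
- **No described analysis uses either label.** This stands. The Data entry and analyses section plans intention-to-treat analysis of all participants with multiple imputation, a mixed model for repeated measures, and sensitivity analyses under missing-at-random and missing-not-at-random assumptions. No completer analysis is described.
- **Withdrawn patients are still followed.** This also stands in large part. The commitment is qualified but real, and an early remitter has not withdrawn consent.

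A reader might infer more: that early remitters erode the dropout allowance and so the power, that the primary comparison is biased, or that a completer analysis would be. The documents support none of these. The label does not delete outcome data, and the primary analysis does not exclude dropouts. A difference between arms would need a difference in how fast patients remit and stop, for which the article gives no figure.

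**Conclusion.** The contradiction is real and is confined to patients who remit and stop before the eighth session. Criterion 1 is wrong as written, because it classifies an early treatment success as a dropout and contradicts the article's own completer definition.

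The consequence is minor. It affects the meaning of the completer and dropout counts, by 0.95 percentage points of an arm's reported dropout rate per patient, and the firmness of these patients' follow-up to Week 12. The primary intention-to-treat analysis is largely protected. The sample size and dropout allowance are unaffected provided these patients are actually assessed. How many patients are involved is unknown, and any total would be a guess.

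The conclusion assumes that some remitters may stop early, which the completer definition implies but no section states outright.

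**What to change.** Add one clause to withdrawal criterion 1: *except patients who stop because of documented remission (HDRS-24 definition under Primary outcome), who are completers and remain on the full assessment schedule through Week 12.* Count and report dropouts by arm on that basis.

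The cost is one clause. The visits through Week 12 are already in Table 1, and neither the sample size nor the analysis model changes.
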